### Study population

Obese patients scheduled for laparoscopic gastric volume reduction surgery under general anesthesia will be screened and recruited during routine preoperative evaluation. Patients are eligible if they meet the following inclusion criteria: 18–60 years old, BMI≥32.5, at the American Society of Anesthesiologists (ASA) Physical Statuses I–III, and at moderate to high risk of developing postoperative pulmonary complications (PPCs). To identify patients at moderate to severe risk for PPCs, the Assess Respiratory Risk in Surgical Patients in Catalonia (ARISCAT) score [9] is applied (see Additional Fig 1). This score predicts individual preoperative risk for developing PPCs with seven predictors, four of which are patient-associated, the other three are surgery-associated. An ARISCAT score ≥26 is related to a moderate to severe risk for PPCs. We use BMI ≥ 32.5 as the standard for morbid obesity under the Asia-Pacific classification [10].

Exclusion criteria are patients aged>60 years or <18 years, ASA grade ≥ IV, with severe chronic obstructive pulmonary disease (COPD, defined as GOLD grades III–IV), having a history of severe or uncontrollable asthma, a history of pulmonary metastasis, in preoperative ongoing renal replacement therapy, with congestive heart failure (defined as NYHA grades III–IV), and failure to be extubated in time after surgery and the need for transference to the ICU with the endotracheal tube.

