### Blinding, data collection, randomization, and record-keeping

This is a single-blind randomized clinical trial. Demographic parameters, intraoperative data, postoperative clinical status, fluid balance, hemodynamic variables, respiratory parameters, anesthesia data, laboratory results, and hygienic indicators will be recorded onto the case report forms (CRF). The information of lung collapse calculated by EIT will be stored in the computer and named with an anonymous number.

All participants meeting the inclusion criteria will be randomized to the Cstat-PEEP group or the EIT-PEEP group in a ratio of 1:1. Randomization will be implemented via a computer-generated blocked randomization form, with 35 blocks of four patients per block. The assignment will proceed with opaque, sealed, and numbered envelopes. Subjects shall be enrolled and allocated in numerical order. All original records (CRF and associated correspondence) will be archived and safeguarded for 10 years and then destroyed, as required by hospital standards.

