**Fig. 3 Fig3:**
[figure not shown]
The ventilator-driven alveolar recruitment maneuver protocol. *Ppeak* peak airway pressure. *Pplat* plateau airway pressure. *PEEP* positive end-expiratory pressure, *Vt* tidal volume normalized for adjusted body weight, *I:E* ratio between inspiratory and expiratory time, *RR* respiratory rate

After the first RM is performed, the individualized PEEP will be titrated by optimal Cstat or EIT according to their grouping information. According to a study conducted by Pereira SM et al. [12], patients in the EIT-PEEP group will be performed an EIT-guided decremental PEEP titration procedure as following (Fig. 4):
After the first RM is performed, immediately after the establishment of pneumoperitoneum, PEEP titration is started. PEEP is started at 20 cmH_2_O and inspiratory pressure at 40 cmH_2_O. PEEP will be decreased at steps of 2 cmH_2_O every 40s, and respiratory rate maintained at 20 breaths/min, inspiratory pause at 30%, and *V*_*T*_ = 6 ml/kg.After the procedure comes to an end, a graph is automatically plotted and displayed by the EIT monitor, which shows the percentage of collapsed and overdistended lung units (equivalent to the percent mass of overdistended or collapsed lung tissue) at each PEEP level.PEEP-EIT is determined as the nearest PEEP above the intersection of the curves representing collapse or overdistension, which indicates a mechanical compromise minimizing both overdistension and collapse of the lung tissue.

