**Fig. 4 Fig4:**
[figure not shown]
EIT-guided individualized PEEP titration. *Paw* airway pressure, *Pplat* plateau airway pressure, *PEEP* positive end-expiratory pressure, *V*_*T*_ tidal volume normalized for adjusted body weight, *RR* respiratory rate, *RM* the ventilator-driven alveolar recruitment maneuver

In the Cstat-iPEEP group, patients’ iPEEP is obtained through the following procedure (Fig. 5):
The first RM (RM1) is performed 5 min after intubation.Limit the peak airway pressure to lower than 55 cmH_2_O.*V*_*T*_ is fixed to 7ml/kg (predicted body weight, PBW), I: E to 1:1, respiratory rate to 12–15 breaths/min.Titration procedure: Immediately after the establishment of pneumoperitoneum, PEEP titration is started. Initial PEEP is set to 5 cmH_2_O. PEEP is increased at steps of 2 cmH_2_O, and each PEEP level is sustained for 3 min, during which Cstat is calculated (in accordance with the formula: Cstat = V_T_ /Plat-PEEP). We end the titration process the moment the calculated Cstat displays a downward trend and choose its previous PEEP (the PEEP that maximizes Cstat) as the optimal PEEP for this patient.The upper limit of PEEP is set to 20 cmH_2_O.After the ideal PEEP is obtained, we perform the second RM2.The third RM3 is performed before extubation.

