Oxygenation index: At before intubation (T0), after the third RM and before extubation (T1), arterial blood is drawn, blood gas analysis is performed, and oxygenation index is calculated.Respiratory parameters: Every 5 min, RR, VT, Ppeak, Pplat, and PEEP are recorded.Blood gas analysis indicators: At before intubation (T0), after the third RM and before extubation (T1), arterial blood is drawn and blood gas analysis is performed.Anesthesia-associated parameters: hemodynamic parameters, recovery time, anesthetic dosage, and occurrence of hypoxemia are recorded constantly.Tertiary outcomes: length of ICU stay, length of hospital stay, costs of treatment, postoperative complications, and other adverse events are recorded.We define PPCs as follows:Mild respiratory failure: PaO_2_/FiO_2_ < 300 or SpO_2_<90%, measured after at least 10 min of breathing room air, but could be alleviated by inhaling supplementary oxygen of 2L/min, hypoventilation excluded.Moderate respiratory failure: PaO_2_/FiO_2_ < 300 or SpO_2_<90%, measured after at least 10 min of breathing room air, but could be alleviated only by inhaling supplementary oxygen>2L/min, hypoventilation excluded.Severe respiratory failure: requiring noninvasive or invasive mechanical ventilation, excluding hypoventilation due to the use of narcotics.ARDS (according to Berlin definition).Bronchospasm (newly detected expiratory wheezing, responding to bronchodilators).New pulmonary infiltrates (new monolateral or bilateral infiltrates demonstrated by chest X-ray, without other clinical signs.)Pulmonary infection (new or progressive radiographic infiltrate plus at least two of the following: requirement of antibiotic treatment, tympanic temperature >38°C, leukocytosis, or leukopenia [white blood cell count <4000 cells/mm^3^ or > 12,000 cells/mm^3^], and/or purulent sputum).Aspiration pneumonitis (respiratory failure resulting from inhalation of regurgitated gastric contents).Pleural effusion (one of the following demonstrated by chest X-ray: blunting of the costophrenic angle, loss of the sharp silhouette of the ipsilateral hemidiaphragm in the upright position, evidence of adjacent anatomical structures displacement, or [in supine position] a hazy opacity in one hemithorax with preserved vascular shadows).Atelectasis (lung opacities with a shift of the hilum, mediastinum, or hemidiaphragm toward the affected area, along with compensatory overdistension in the adjacent nonatelectatic lung).Cardiopulmonary edema (clinical signs of congestion, including dyspnea, edema, rales, and jugular venous distention, with chest X-ray demonstrating an increase in vascular markings and diffuse alveolar interstitial infiltrates).Pneumothorax (air in the pleural cavity, without vascular bed around the visceral pleura).

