### Statistical analysis

After completing the trial, the research team will collaborate with medical statisticians to analyze the data. Statistical analysis will be performed on the basis of intention to treat. SPSS 20.0 software will be used for analysis. The majority of data will be collected and recorded onto the CRF. Before analyzing the data, the pattern of missing data will be evaluated. Analyzation of graphics and data acquired from the EIT machine will be executed by a computer expert familiar with machine principles. Kolmogorov-Smirnov analysis will be used to detect the distribution of all the data. Normally distributed data will be expressed by the mean and standard deviation (SD), while skewed data will be expressed by their median and interquartile range. Unpaired *t* test will be used for univariate analysis of normally distributed data. Pearson correlation test will be employed to test the correlation between two variables. Mann-Whitney *U* test and Wilcoxon signed-rank test will be applied for skewed data. Categorical variables will be assessed by Fisher’s exact test, chi-square tests, or relative risk, if appropriate. 95% CI will be employed to express statistical uncertainty. *P* value <0.05 shall be regarded as significant.

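### Failed extubation with intubated transfer to the ICU is listed as an exclusion criterion, although it can occur only after randomisation and the assigned titration, and this conflicts with intention to treat

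*Protocol article*

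**What the plan says.** The exclusion list in Study population combines baseline conditions (age, ASA grade, severe COPD, severe asthma, heart failure and others) with one item of a different kind: "failure to be extubated in time after surgery and the need for transference to the ICU with the endotracheal tube".

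The same section says that patients "will be screened and recruited during routine preoperative evaluation". The section on blinding, data collection and randomization says "All participants meeting the inclusion criteria will be randomized to the Cstat-PEEP group or the EIT-PEEP group in a ratio of 1:1". Under Intervention, after the first recruitment maneuver, "the individualized PEEP will be titrated by optimal Cstat or EIT according to their grouping information". For the Cstat arm, "Immediately after the establishment of pneumoperitoneum, PEEP titration is started", and the EIT arm starts at the same point.

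On the analysis population, Statistical analysis says "Statistical analysis will be performed on the basis of intention to treat". Study endpoints counts as a pulmonary complication "Severe respiratory failure: requiring noninvasive or invasive mechanical ventilation", and the same item then sets aside hypoventilation caused by narcotics. It also lists "Tertiary outcomes: length of ICU stay, length of hospital stay", together with costs and complications. The primary endpoint is EIT-measured collapse immediately after extubation and 2 h after surgery.

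**The concern.** An eligibility criterion should be decidable before allocation. This one is decided at the end of surgery, after the patient has received one of the two PEEP strategies under comparison, and the strategy may influence it. Excluding on it conditions the comparison on a post-treatment event, so the retained groups are no longer the randomised groups.

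The design makes this more serious. The trial tests non-inferiority of Cstat titration, and its hypothesis (Background) covers pulmonary complications as well as atelectasis. If the Cstat strategy led to more failed extubations, the criterion would remove that evidence from the primary comparison, the complication count and ICU stay together. The error would favour the claim under test.

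The article also does not define what counts as timely extubation. Only the assessor is described as blinded, and the staff who titrate PEEP necessarily know the arm. A judgement made with knowledge of the arm could therefore decide who stays in the trial.

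**Working it through.** **Order of events.**
1. Recruitment is preoperative (Study population).
2. Randomisation follows for those who meet the inclusion criteria. Its exact moment is not given, but it must precede titration, because titration follows the allocated group.
3. Titration starts at pneumoperitoneum, during surgery (Intervention).
4. Extubation, or failure to extubate, comes after surgery.

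The exclusion depends on step 4 and can act only on patients who have passed steps 2 and 3. Intention to treat keeps every patient who passed step 2. Both statements cannot be applied together. Study dropouts mentions withdrawal of consent and termination by an investigator, but not this event, so it does not resolve the conflict.

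**Overlap with outcomes.** Continued invasive ventilation meets the severe respiratory failure item unless it is due to narcotic-related hypoventilation. An intubated ICU transfer contributes to ICU stay whatever its cause.

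**Size.** The plan has no figure for failed extubation to reproduce, so what follows is illustration. From Sample size calculations: expected collapse 6.5% (Cstat) and 6.2% (EIT), difference 0.3 points, margin 2 points, 70 patients per group. Assumed: k Cstat patients fail extubation, each would have had X% collapse, and the remaining Cstat patients average 6.5%.

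Shift in the Cstat mean when these patients are counted = k × (X − 6.5)/70.

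With k = 3 in the Cstat arm and none in the EIT arm:

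| X | Shift (points) | All-randomised difference | Shift as share of margin |
|---|---|---|---|
| 11% | 3 × 4.5/70 = 0.19 | 0.49 | 10% |
| 20% | 3 × 13.5/70 = 0.58 | 0.88 | 29% |
| 30% | 3 × 23.5/70 = 1.01 | 1.31 | 50% |

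The 11% is the non-ventilated share that the Discussion cites for obese patients under anesthesia and ventilation. The 20% and 30% are assumptions.

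- One failure per arm at 20%: the Cstat mean moves by 13.5/70 = 0.193 and the EIT mean by 13.8/70 = 0.197, a net change of about zero.
- Three failures in the EIT arm only, at 20%: the EIT mean rises by 3 × 13.8/70 = 0.59 and the all-randomised difference becomes 0.3 − 0.59 = −0.29. Here exclusion works against Cstat.
- Complications: three of 70 is 4.3 percentage points, if all three meet the definition.

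**Could the conclusion change?** No SD is stated. Reading the 0.025 as one-sided, 64 per group implies SD = (2 − 0.3) × √(64/2)/(1.960 + 0.842) = 3.43.

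- Three Cstat patients excluded (67 v 70): upper limit = 0.3 + 1.96 × 3.43 × √(1/67 + 1/70) = 1.45, below 2.
- Included (70 v 70): the Cstat variance becomes (67/70) × 3.43² + (67 × 3/70²) × (X − 6.5)². At X = 11% the SD is 3.48 and the limit is 0.49 + 1.96 × 0.584 = 1.64, still below 2. At X = 20% the SD is 4.33 and the limit is 0.88 + 1.96 × 0.661 = 2.17, above 2.

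Under the 3 v 0 split, whether the conclusion changes depends on the assumed collapse value.

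**The case against.** The strongest reply is that no text says these patients leave the analysis set. The item stands in an eligibility list, the analysis section promises intention to treat, and the CONSORT diagram, which is not shown, might bear on the point. That is fair as far as it goes: no removal is reported, and none should be presumed. It does not resolve the conflict. An exclusion criterion that can act only after treatment has no other function than to take patients out, and nothing in the text says that they stay.

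Three further objections stand and limit the point.

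- A reader might infer that the criterion removes the patients with the worst lungs. The documents do not support this. The criterion names no cause, and the severe respiratory failure item itself sets aside narcotic-related hypoventilation. Some of these patients would count as pulmonary complications and some would not.
- A reader might infer that exclusion necessarily pulls the arms together. It does so only if failures are more frequent or worse in the Cstat arm. Balanced failures change almost nothing, and an excess in the EIT arm reverses the direction.
- A patient still intubated has no value immediately after extubation, and a 2 h EIT reading during ventilation is not the same quantity as in extubated patients. An available scan therefore cannot simply be substituted. This calls for a stated handling rule, whose detail may sit in an analysis plan that is not shown. It does not justify exclusion.

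**Conclusion.** The point holds in limited form. The exclusion depends on an event after randomisation and treatment, contradicts the stated intention-to-treat analysis, and can delete events that count as complications or ICU stay. This follows from the text alone and needs no assumption beyond randomisation preceding titration, which the text implies.

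The effect on the result is unknown in size and direction. With three failures in the Cstat arm and none in the EIT arm, the mean difference shifts by 0.19 to 1.0 points for assumed collapse of 11% to 30%, against a 2-point margin. With balanced failures it shifts by about zero. A reader might infer that the criterion would reverse the trial's conclusion. Scenarios can be built in which it does (20% collapse) and in which it does not (11%), and the documents give neither the event rate nor the collapse values needed to choose between them. The case for correction rests on the contradiction and on the possible bias in a non-inferiority comparison, and not on any one scenario.

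**What to change.** 1. Delete the item from the exclusion criteria.
2. State that every randomised patient stays in the intention-to-treat set, including any patient already excluded on this ground. The article describes the trial as ongoing, so this may still be possible.
3. Report failed extubation with intubated ICU transfer by arm.
4. Count it as severe respiratory failure only where it meets the definition in Study endpoints, including the narcotic exception, and include the resulting ICU stay.
5. For the primary endpoint, treat it as an intercurrent event. Specify, before the data are analysed, how the missing post-extubation EIT value is handled, and add a sensitivity analysis, for example one that assigns the worst observed collapse value.

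The cost is a short amendment and one additional analysis. The downside is that a few patients will carry an imputed primary value, which is why the sensitivity analysis is needed.

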### Standard procedures

To avoid interfering the trial intervention, components of perioperative anesthesia care (involving general anesthesia, postoperative analgesia, and fluid management) are performed by a fairly fixed team of anesthesiologists in accordance with the clinical routine. The following strategies are recommended:
Before surgery, all patients need a thorough assessment of the airway, performed on the basis of 12 predictors of a difficult airway. When more than three of the predictors are present, endotracheal intubation is performed when patients are awake or after slow induction while maintaining spontaneous breathing should be taken into consideration. Adequate equipment, personnel, and medicine required for artificial airway establishment should be prepared in advance (see Additional Table 1: Predictors of Difficult Airway).According to clinical routine, upon admission to the operation room, patients’ following parameters are monitored: electrocardiogram, non-invasive blood pressure, BIS, pulse oximetry, and urine output. Invasive arterial blood pressure is continuously measured after the insertion of an arterial line into the radial or dorsal pedis artery under regional anesthesia.After intravenous and arterial catheterization, an EIT belt will be placed at the fifth intercostal space, and continuous EIT monitoring (PulmoVista 500, Drager) will be started.For patients without predicted difficult airway, anesthesia induction is performed using rapid sequence induction: 0.05mg/kg midazolam is given to patients 15 min before induction; sufentanil, etomidate, rocuronium, or cisatracurium are used for induction. Mechanical ventilation is initiated after endotracheal intubation.Total intravenous anesthesia is applied for the maintenance of anesthesia with propofol and remifentanil.Intraoperative hemodynamics is managed in accordance with surgical procedure and blood loss.Performing postoperative analgesia to ensure a VAS pain score<3. Regional anesthesia or neuraxial block should be applied whenever indicated.Postoperative physiotherapy involving early mobilization and stimulation of cough along with deep breathing exercises should be performed.

Data related to the procedures applied shall be collected in detail and analyzed. Anesthesia care and associated treatment must abide by clinical routines. Intravenous catheters and nasogastric tubes may be used in accordance with guidelines or surgical practice. Urinary bladder catheters are usually not applied routinely for this sort of surgery in our hospital.

### Mechanical ventilation

The following are ventilator settings: We set the driving pressure to 15cmH_2_O, using pressure-control-volume compensation mode (PSV-VC). The lowest possible fraction of inspired oxygen is used (FiO_2_ ≥0.4) to avoid hypoxemia (defined as SpO_2_ >92%). The compensated tidal volume is fixed at 7ml/kg (PBW), and the respiratory rate is set to 12–15 times/minute (adjusted to normocapnia, defined as P_ET_CO_2_ maintained at 35–45 cmH_2_O). Management of anesthesia maintenance is left to the discretion of the anesthesiologist in charge. All complications related to anesthesia are managed in accordance with clinical guidelines.

### Intervention

After endotracheal intubation, and initiation of mechanical ventilation PEEP is maintained at 5cmH_2_O for 5 minutes, baseline parameters are measured and recorded in all patients during this period. All patients (in both groups) are submitted to ventilator-driven alveolar recruitment maneuvers (RM) 5 min after endotracheal intubation [11], and then, the same procedure is repeated after finishing PEEP titration and before extubation (Fig. 2).

**Fig. 2 Fig2:**
[figure not shown]
Individualized PEEP and perioperative management process. *iPEEP* individualized positive end-expiratory pressure, *Cstat-iPEEP* optimal static lung compliance-directed iPEEP titration group, *EIT-iPEEP* electrical impedance tomography-guided iPEEP titration group, *RM* the ventilator-driven alveolar recruitment maneuver

RM is performed in the following steps (Fig. 3):
In pressure-controlled ventilation, driving pressure is restrained within 15cmH_2_O.Increase PEEP from 5 to 20 cmH_2_O with 5 cmH_2_O raise each time and keep PEEP constant for 30s after each increase. When PEEP reaches 20 cmH_2_O, resulting in an inspiratory pressure of 40 cmH_2_O, maintain 5 breathing circles at PEEP 20 cmH_2_O until the end.Throughout the duration of the RM, VT is set to 7ml/kg, and I:E is set to 1:1.Ppeak <55 cmH_2_O.All patients receive a standardized fluid regimen along with vasopressors during the RM maneuver according to the protocol to alleviate short-term hemodynamic suppression caused by RM and maintain MAP ≥ 65 mmHg.

**Fig. 3 Fig3:**
[figure not shown]
The ventilator-driven alveolar recruitment maneuver protocol. *Ppeak* peak airway pressure. *Pplat* plateau airway pressure. *PEEP* positive end-expiratory pressure, *Vt* tidal volume normalized for adjusted body weight, *I:E* ratio between inspiratory and expiratory time, *RR* respiratory rate

After the first RM is performed, the individualized PEEP will be titrated by optimal Cstat or EIT according to their grouping information. According to a study conducted by Pereira SM et al. [12], patients in the EIT-PEEP group will be performed an EIT-guided decremental PEEP titration procedure as following (Fig. 4):
After the first RM is performed, immediately after the establishment of pneumoperitoneum, PEEP titration is started. PEEP is started at 20 cmH_2_O and inspiratory pressure at 40 cmH_2_O. PEEP will be decreased at steps of 2 cmH_2_O every 40s, and respiratory rate maintained at 20 breaths/min, inspiratory pause at 30%, and *V*_*T*_ = 6 ml/kg.After the procedure comes to an end, a graph is automatically plotted and displayed by the EIT monitor, which shows the percentage of collapsed and overdistended lung units (equivalent to the percent mass of overdistended or collapsed lung tissue) at each PEEP level.PEEP-EIT is determined as the nearest PEEP above the intersection of the curves representing collapse or overdistension, which indicates a mechanical compromise minimizing both overdistension and collapse of the lung tissue.

